## Abstract

**Background:**

Caregivers to a person diagnosed with a glioblastoma often face significant responsibilities, balancing the demands of care with the complexities of the disease and treatment trajectory, while also coping with concerns and uncertainty of the future. Caregivers report unmet needs of information and support throughout the patient’s disease and treatment trajectory, and they may benefit from targeted supportive care interventions.

**Objective:**

The aim of this study is to develop, test, and evaluate the feasibility of a supportive group intervention among caregivers to patients diagnosed with a glioblastoma.

**Methods:**

The study consists of 3 phases with ongoing patient and public involvement (PPI). In the first phase, a systematic review will be carried out exploring the outcome of supportive group interventions for caregivers to patients diagnosed with a primary brain tumor. In the second phase, the design and development of the intervention will be conducted in cooperation with a panel of caregivers using PPI process. The third phase will include the feasibility and evaluation of the intervention. The study will be guided by the British Medical Research Council’s framework for developing complex interventions. The feasibility of the intervention will be tested in reference to relevant parameters. Quantitative data in terms of questionnaires will be analyzed using descriptive statistics, and qualitative evaluation interviews will be analyzed using thematic analysis.

**Results:**

A national panel of caregivers (N=10) has been established, and the final design of the intervention is currently developed through an ongoing PPI process. A total of 3 hospitals in Denmark have committed to participating in the recruitment for the feasibility study. Recruitment began in April 2025, and the SUGRI (Supportive Group Intervention for caregivers to patients diagnosed with a glioblastoma) intervention will undergo a feasibility assessment in a multicenter study starting in August 2025, with the final evaluation planned for April 2026.

**Conclusions:**

This study is expected to provide necessary insights to guide caregiver initiatives, ultimately improving support for caregivers within the neuro-oncology field. A supportive group intervention offered to the caregivers has the potential to address specific caregiver needs and strengthen their supportive network. Providing caregivers with support may enhance their perceived support, strengthen family functioning, and provide them with strategies to manage caregiving challenges, ultimately benefiting both caregivers and patients.

**Trial Registration:**

ClinicalTrials.gov NCT06869577; https://clinicaltrials.gov/study/NCT06869577

**International Registered Report Identifier (IRRID):**

PRR1-10.2196/81948

## Introduction

Primary malignant brain tumors are among the most fatal cancers and have an international incidence rate of 6.89 per 100,000, compared with 7.03 per 100,000 in Denmark [1,2]. The most common malignant brain tumor is a glioblastoma (GBM), accounting for 51.5% of all malignant brain tumors. It is associated with a poor prognosis: a 5-year relative survival rate of 5% [1]. The typical disease trajectory of 12 to 15 months includes initial surgical intervention (resection or biopsy), followed by a 9- to 10-month standard treatment plan consisting of concomitant chemotherapy or radiation therapy, with subsequent adjuvant chemotherapy of temozolomide [3]. Despite aggressive treatment, tumor progression occurs almost inevitably [4].

The diagnosis of a GBM is usually preceded by symptoms such as an epileptic seizure, focal neurological deficits, or cognitive changes that may affect the patient’s functional status [2]. Patients often develop a complex symptom burden, including physical symptoms such as aphasia and hemiparesis and psychological symptoms such as cognitive deficits, anxiety, distress, and depression. The symptoms may change as tumor progresses [5-7]. The combination of a rapid onset of the disease, the intense disease and treatment trajectories, and the uncertainty of the future affect not only the individual but also those close to them who function as informal caregivers, a role that often demands great caring responsibilities [8,9]. The caregiver burden is described as multidimensional with components affecting caregivers physically, emotionally, socially, and economically [10]. Caregivers express being unprepared for the new role and report symptoms of anxiety and depression [4,9]. Additionally, social isolation is often a consequence of the caregiver role. Furthermore, the *invisibility* of the patients’ symptoms can lead to withdrawal of support from family and previous networks [4,11]. Caregivers emphasize the importance of meeting other caregivers in similar situations so that they can share experiences and recognize emotions or concerns in a peer-to-peer environment [12,13]. Peer support may represent an important access to information, advice, and practical help for caregivers and address caregivers’ individual needs of support [12,14,15]. It is often a struggle for caregivers to be separated from the patient, as they worry about risk of seizures or cognitive symptoms that necessitate constant supervision, a struggle that can be alleviated with support [16]. Online access to peer support and information may be valuable for caregivers. Such a tool is accessible and has the potential to ensure broad reach while remaining scalable at the national level. Moreover, online support aligns well with the recommendations of the International Council of Nurses, which indicate that digital health can address population needs, strengthen health systems, and remain feasible despite shortages in the health workforce [17].

Several authors address the lack of longitudinal studies and advocate for ongoing supportive interventions to target caregivers of patients diagnosed with a brain tumor [10,18,19]. A need of such interventions is further echoed in international research agendas [20,21]. A systematic review from 2021 concluded feasibility of interventions for people with a brain tumor and their caregivers [14]. Importantly, support groups exclusively for caregivers may fulfill their need for peer support [14,22]. Therefore, this study aims to develop, test, and evaluate the feasibility of a supportive group intervention among caregivers to patients diagnosed with a GBM.

## Methods

### Study Design

This study titled SUGRI (Supportive Group Intervention for caregivers to patients diagnosed with a glioblastoma) is a 3-phase study. The overall framework is guided by the British Medical Research Council (MRC) framework for developing complex intervention. This methodological framework entails 4 main phases of intervention research: development or identification of the intervention, feasibility, evaluation, and implementation. In this study, we develop, test, and evaluate the feasibility of an intervention; therefore, we are primarily guided by the first 2 phases of the MRC framework: the development phase and the feasibility phase [23-25]. The phases of the MRC framework applied to the SUGRI study are presented in Figure 1. An overview of the intervention logic, including planned activities and expected outcomes, is presented in Figure 2. A patient and public involvement (PPI) plan will be carried out throughout all phases of the SUGRI study, guided by the workbook to guide the development of a Patient Engagement in Research plan [26]. The recommended checklist for research protocols, SPIRIT (Standard Protocol Items: Recommendations for Interventional Trials), has been applied (Multimedia Appendix 1) [27].

**Figure 1 figure1:**
[figure not shown]
Complex intervention for the SUGRI (Supportive Group Intervention for caregivers to patients diagnosed with a glioblastoma) study. Solid lines represent this study’s activities; dashed lines represent planned future activities. HCP: health care professional.

**Figure 2 figure2:**
[figure not shown]
Logic model. Solid lines represent planned work; dashed lines represent intended results. HCP: health care professional; PEIR: Patient Engagement in Research; PPI: patient and public involvement; REDCap: Research Electronic Data Capture; SUGRI: Supportive Group Intervention for caregivers to patients diagnosed with a glioblastoma.

### Study Population and Eligibility Criteria

The term “caregivers” is in this study defined according to the criteria provided by The National Cancer Institute [28]: “Informal caregiving is broadly defined as services provided by an unpaid person, such as helping with personal needs and household chores, managing a person’s finances, arranging for outside services, or visiting regularly. An informal caregiver is usually a relative or friend who may or may not live in the same household as the person with cancer who requires care.” Inclusion criteria are family caregivers (aged ≥18 years) to patients (aged ≥18 years) diagnosed with a GBM grade 4 or diffuse astrocytoma grade 4 receiving chemoradiotherapy treatment. Despite differential terminology of GBM grade 4 and diffuse astrocytoma grade 4 since 2021 [29], the study will include both categories of grade 4 tumors; both are referred to as “GMB” in the protocol. Participants must be able to understand, read, and speak Danish.

### Recruitment Procedure

Participants will be recruited from the Department of Neuro-oncology at Copenhagen University Hospital in Denmark. The feasibility of the intervention is planned to be evaluated nationally, and the 3 other departments of neuro-oncology in Denmark at Odense University Hospital, Aarhus University Hospital, and Aalborg University Hospital will be invited to participate in the recruitment procedure. A purposive sampling strategy will be applied, and participants will be recruited face-to-face.

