#### Feasibility and Evaluation Phase

The feasibility phase in the MRC framework includes assessment of the feasibility and acceptability of the intervention. It also involves evaluation of the design and the predefined feasibility parameters, addressing uncertainties identified during development, refining the intervention, and considering practical and economic aspects [25]. In the third study phase, the online intervention will be tested on a new group of caregivers, and feasibility will be analyzed and evaluated by integration of qualitative and quantitative methods. A sample size of approximately 30 participants is recommended for feasibility trials [37].

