Feasibility and evaluation phase	Feasibility study	Aim: to test the feasibility of a supportive group intervention among caregivers to patients diagnosed with a glioblastoma Primary assessment: predefined feasibility parameters: Recruitment: is it feasible to recruit participants to the intervention? Fidelity: is the intervention provided as designed? Adherence: how feasible is it to ensure participants adhere to the intervention? Acceptability: what are the experiences and ratings of satisfaction with the intervention? Safety: is the intervention safe for participants?	Qualitative data: semistructured individual interviews with caregivers Quantitative data: patient- and caregiver-reported outcome Quantitative registration of recruitment rate Participants are offered the intervention Quantitative registration of intervention participation and participant feedback via study-specific questionnaires and interviews Participant feedback via study-specific questionnaires and interviews Adverse events from validated questionnaires and interviews	Proceed to development of a stepped care model if: All 5 feasibility parameters meet their predefined benchmarks Estimated recruitment ≥60%c Estimated fidelity 100%c Estimated adherence ≥70%c Estimated acceptability mean ≥4d Safety reported narrativelye

^a^PRISMA: Preferred Reporting Items for Systematic Reviews and Meta-Analyses.

^b^PPI: patient and public involvement.

^c^Recruitment rate, fidelity, and adherence are presented as estimates informed by other caregiver interventions and reported as percentages.

^d^Acceptability is defined as an average score of ≥4 on a 5-point Likert scale in a study-specific questionnaire. The questionnaire includes the item: “Overall, I found the caregiver program to be supportive,” rated from 1=not at all to 5=to a very great extent.

^e^Safety will be reported narratively based on individual postintervention evaluation interviews with caregivers, guided by the following question: “Have you experienced any concerns as a result of your participation that you did not have before?”

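### Participants are enrolled by purposive sampling, so the 60% recruitment benchmark depends on whom recruiters approach and cannot be read as uptake among eligible caregivers

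*Protocol article*

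**What the plan says.** The sampling method is in Methods, Recruitment Procedure: "A purposive sampling strategy will be applied, and participants will be recruited face-to-face". It is stated for participants in general, not only for interviewees. The characteristics that guide the selection are not given there.

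The eligible population is set separately, under Study Population and Eligibility Criteria: "Inclusion criteria are family caregivers (aged ≥18 years) to patients (aged ≥18 years) diagnosed with a GBM grade 4 or diffuse astrocytoma grade 4", with the patient receiving chemoradiotherapy.

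Recruitment is the first feasibility parameter listed under the primary objective. For it, Table 1 (Primary Objective and End Points) gives:

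- the question: "Recruitment: is it feasible to recruit participants to the intervention";
- the measurement: "Quantitative registration of recruitment rate";
- the benchmark: "Estimated recruitment ≥60" per cent;
- its basis, in a footnote: "Recruitment rate, fidelity, and adherence are presented as estimates informed by other caregiver interventions and reported as percentages";
- its role, as a condition for moving on: "All 5 feasibility parameters meet their predefined benchmarks".

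On size, the Feasibility and Evaluation Phase section says: "A sample size of approximately 30 participants is recommended for feasibility trials". The Results section reports that recruitment began in April 2025.

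**The concern.** A recruitment percentage answers the question in Table 1 only if the people in its denominator were not picked by those whose success it measures. Purposive sampling gives recruiters discretion over who is asked. It is a sound way to choose informants for interviews, but a poor basis for an uptake rate held against a fixed threshold.

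At stake is one of the five conditions for progression. The study could record a pass on recruitment although most eligible caregivers would decline. It could also record a failure although they would accept. The published rate would not show which of these had happened.

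**Working it through.** **The plan's own figure.** There is nothing to reproduce. The 60% is informed by other caregiver interventions, and the sample of about 30 is a cited recommendation. Together they imply only that 30 enrolled at exactly 60% corresponds to 30 / 0.60 = 50 caregivers in the denominator.

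**Set-up.** Let

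- f = share of eligible caregivers who are approached;
- u1 = uptake among those chosen;
- u0 = uptake that those not chosen would have had.

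Three different quantities could then be called the recruitment rate:

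- consented / approached = u1;
- consented / eligible = f × u1;
- uptake had all eligible caregivers been asked = f × u1 + (1 − f) × u0.

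The third is the one that answers the question in Table 1.

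**Illustration.** All inputs are assumed, because the article gives no counts: u1 = 70%; f = 30%, 50% or 70%; u0 = 20%, 40% or 70%.

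| f | Consented / approached | Consented / eligible | All asked, u0 = 20% | All asked, u0 = 40% | All asked, u0 = 70% |
|---|---|---|---|---|---|
| 30% | 70% | 21% | 35% | 49% | 70% |
| 50% | 70% | 35% | 45% | 55% | 70% |
| 70% | 70% | 49% | 55% | 61% | 70% |

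Example for the first row: 0.3 × 0.7 + 0.7 × 0.2 = 0.21 + 0.14 = 0.35.

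**Approached as denominator.** The benchmark is passed at 70% in every row. In the six cases where those not chosen are less willing (u0 = 20% or 40%), uptake had all been asked is below 60% in five.

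**The opposite direction.** Suppose selection aims for variation and reaches less willing caregivers. With u1 = 40%, u0 = 70% and f = 30%, the approached-based rate is 40% and fails. Uptake had all been asked would be 0.3 × 0.4 + 0.7 × 0.7 = 0.12 + 0.49 = 61%, which passes.

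**Eligible as denominator.** The rate is 21%, 35% or 49% and fails in every row. This includes the last column, where everyone would have consented at 70%. The failure there comes from not asking, not from refusal.

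**Consecutive approach.** With f = 1 all three quantities equal u1, and the benchmark can be read directly. Only sampling error is left: 30 of 50 has an exact 95% interval of 45% to 74%.

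**The case against.** The strongest reply is that purposive may mean no more than recruiting people who meet the inclusion criteria, and that a journal article condenses the approach procedure, the log and the denominator. The second half stands: missing detail on denominator or log is not the point here, and it cannot be inferred that no log is kept. The first half does not remove the conflict. If all eligible caregivers are in fact approached, the word is wrong and the same sentence needs correcting.

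It is also fair to say that the selection effect vanishes if those not chosen are just as willing and the denominator is those approached. That is true (last column of the table), but the design gives no means of checking it.

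A reader might infer several stronger claims that the article does not support:

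- *The rate is biased upward.* Nothing says that recruiters pick likely acceptors, and sampling for variation could lower the rate.
- *Selective approach alone can secure the decision to proceed.* It cannot: fidelity, adherence, acceptability and safety are also required.
- *Enrolling 30 when 100 are eligible shows 30% uptake.* Those counts are not in the article, and such a figure mixes people never asked with people who refused.
- *Face-to-face contact excludes the very caregivers the online format is for.* Some caregivers who do not attend may be missed, but the article does not name them as the target group, and many probably attend with the patient. This is secondary at most.
- *The rate is meant to plan a later trial.* Table 1 ties the benchmarks to developing a stepped care model.

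**Conclusion.** The point holds in a limited form. A judgement-based sample and a fixed recruitment percentage used as a condition for progression are both stated, and they do not fit together. Under either natural denominator, approached or eligible, the rate depends on the recruiters' choices and cannot be read as uptake among eligible caregivers.

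The direction and size of the distortion are unknown. The percentages in the working show what can happen under assumed inputs and are not estimates for this study. One of the five progression criteria is directly affected, and no sample-size or power figure changes.

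The conclusion assumes that the rate is a share of caregivers approached or eligible. If it is a share of a recruitment target, it is not an uptake measure at all, and the plan should say so.

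**What to change.** 1. For enrolment, replace purposive sampling with consecutive approach of all eligible caregivers at each participating department during the recruitment window.
2. Record the numbers eligible, approached and consented, with reasons for non-approach and for refusal.
3. Judge the 60% on consented / approached under consecutive approach, or on whichever denominator the benchmark's source literature used. Report approached / eligible and consented / eligible beside it.
4. Report caregivers already recruited purposively since April 2025 separately, or reconstruct their counts where possible.
5. Keep purposive selection, if wanted, for the qualitative interviews only.

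The cost is one amended sentence, a defined denominator and routine record keeping at the departments. The downside is less control over the diversity of the sample and possibly a lower stated recruitment rate.

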### Study Phases

#### Exploratory Phase

A systematic review will identify and explore available evidence of outcomes of supportive group interventions for caregivers to patients diagnosed with a primary brain tumor. To define the group element of an intervention, we decided to include “any kind of intervention, that sought to facilitate some element of interaction between a minimum of two caregivers.” The search will be conducted in the following databases: PubMed, Embase, Web of Science, Emcare, Cochrane Library, and PsycInfo. Peer-reviewed studies in English, German, or Scandinavian will be included without any time limits. The software program Covidence (Veritas Health Innovation Ltd) will support the process of screening [30]. Guidance on the conduct of narrative synthesis in systematic reviews will be used to interpret findings [31]. To address the quality of the included studies, the Mixed Methods Appraisal Tool will be applied [32]. To ensure transparency, the PRISMA (Preferred Reporting Items for Systematic Reviews and Meta-Analyses) guideline will be used [33].

#### Development Phase

According to the MRC framework, the development phase focuses on designing the intervention based on existing evidence and relevant theories, engaging stakeholders, and refining the intervention to ensure contextual fit and relevance to the target population [25]. Therefore, the development of the SUGRI intervention will be grounded in existing evidence from the neuro-oncology field, informed by the findings from the systematic review, and be carried out in close collaboration with stakeholders.

#### PPI Activities

PPI will be central in the development phase, where a national panel of current and bereaved caregivers to patients with a GBM will be established. A panel consisting of 6 to 12 members will allow for deeper interaction and a more trusting environment. Members will be recruited nationally through the Danish Brain Tumor Association. The intervention will be developed and designed in collaboration with a panel of caregivers, using Microsoft Teams as the meeting platform. Online meetings will be scheduled for every second month, and 1 cocreative workshop requiring physical attendance will be planned and facilitated in cooperation with the Danish Knowledge Center for User Involvement in Health Care. The PPI process will be evaluated through a focus group interview with the panel members, guided by the approach described by Krueger and Casey [34]. For the quantitative evaluation, the 22-item Patient Engagement in Research Scale will be used to measure the level of meaningful caregiver engagement in the research process [35,36].

#### Intervention

The intervention will be conducted online and will encompass 2 primary components: an informational element and a group-based element. The final design of the intervention and how the 2 central elements will be incorporated will be developed through an iterative PPI process in cooperation with the panel to integrate existing evidence on caregivers’ needs and preferences. Results from the systematic review from the exploratory phase will also guide the design of the final intervention. The group element will be designed and inspired by existing knowledge of caregiver preferences of supportive group interventions [11,22].

#### Feasibility and Evaluation Phase

The feasibility phase in the MRC framework includes assessment of the feasibility and acceptability of the intervention. It also involves evaluation of the design and the predefined feasibility parameters, addressing uncertainties identified during development, refining the intervention, and considering practical and economic aspects [25]. In the third study phase, the online intervention will be tested on a new group of caregivers, and feasibility will be analyzed and evaluated by integration of qualitative and quantitative methods. A sample size of approximately 30 participants is recommended for feasibility trials [37].

